## Abstract

**Background:**

Many studies have shown the potential therapeutic effect of acupuncture on allergic rhinitis. Most of these studies were limited by low-quality evidence. Preliminary experiments showed that the use of acupuncture at three nasal acupoints plus acupoint application (AAP) achieves a more persistent effect in the treatment of perennial allergic rhinitis than acupuncture alone. In this study, a multicenter, single-blind, randomized controlled trial will be performed, in which acupuncture at nonmeridian acupoints and sham AAP will be used as the control group to evaluate the effect of AAP through long-term observation.

**Methods:**

The trial is designed on the basis of the Consolidated Standards of Reporting Trials 2010 guidelines and Standards for Reporting Interventions in Controlled Trials of Acupuncture. A total of 120 participants with perennial allergic rhinitis will be randomly assigned to a treatment or control group. A specially appointed investigator will be in charge of randomization. The participants in the treatment group will be treated with acupuncture at EX-HN3, LI20, and EX-HN8 thrice per week for a total of 12 sessions. In addition, they will undergo AAP at DU14, BL13, EX-BI, and RN22. The participants in the control group will be treated with sham AAP. The primary outcome will be the change in the Total Nasal Symptom Score from baseline to the completion of 4-week treatment. Secondary outcomes include changes in visual analog scale and total non-nasal symptom scores from baseline to the second and fourth weeks of treatment, as well as 1, 3, and 6 months after the completion of treatment. Peripheral blood IL-4, IL-5, IL-6, IL-8, and IL-10 levels will be measured, and any side effects related to treatment will be observed and recorded.

**Discussion:**

It is expected that this randomized clinical trial will provide evidence to determine the effects of AAP compared with acupuncture at nonmeridian acupoints and sham AAP, particularly the long-term effect. These findings will help improve the clinical application of this technique.

**Trial registration:**

Acupuncture-Moxibustion Clinical Trial Registry AMCTR-ICR-18000179. Registered on 12 April 2018.

## Background

Allergic rhinitis (AR) is a symptomatic nasal disorder resulting from an IgE-mediated immunological reaction to allergen exposure [1]. The clinical manifestation of AR includes rhinorrhea, nasal pruritus, nasal obstruction, and excessive sneezing. Other associated symptoms include postnasal drip, ocular pain, headache, and insomnia. AR has adverse impacts on sleep, cognitive functioning, mood, and other associated comorbidities such as asthma and sinusitis, ultimately affecting quality of life, as well as work and school performance [2]. According to epidemiological research findings, AR affects up to 40% of the global population [3, 4] and 11.1–17.6% of the Chinese population [5], affecting the quality of life of patients [6] and causing a significant socioeconomic burden [7]. Proper classification facilitates selecting the most appropriate treatment strategies for AR patients [1, 8, 9]. AR may be classified by (i) temporal patterns of exposure to trigger allergens such as seasonal (e.g., pollens), perennial/year-round (e.g., dust mites), and episodic allergens (e.g., irregular environmental exposures such as visiting a home with pets); (ii) frequency of symptoms; and (iii) severity of symptoms. AR severity can be classified from mild (when symptoms are present but do not interfere with quality of life) to more severe (when symptoms interfere with quality of life) [10]. The pathogenesis of AR can be divided into four phases: sensitization, subsequent reaction to allergen, late-phase activation, and systemic activation [9].

Controlling symptoms has traditionally been the main goal of AR management due to elusiveness of definitive cure [11]. The current mainstream AR managements include avoidance of allergens and other trigger factors, pharmacotherapy, immunotherapy, and desensitization. Despite the methodological limitations in the few economic evaluations that have been conducted, evidence appears to support the cost-effectiveness of subcutaneous immunotherapy rather than of pharmacotherapy [12]. However, these treatments do not always provide complete symptom relief and are associated with undesirable side effects. Pharmacotherapy provides only rapid symptom relief from perennial AR (PAR) and becomes less effective when recurrently used due to the development of drug tolerance [13, 14].

Complementary and alternative medicine (CAM) therapies, including Chinese herbal medicine, Ayurvedic medicine, other single and multiple herbal preparations, acupuncture, homeopathy, and several other modalities, continue to gain popularity in the treatment of AR. Reportedly, > 42% of Americans have used CAM for AR, and the popularity of CAM therapies for allergic diseases is even greater in some European countries [15, 16]. A hospital survey conducted in Japan found that 19.2% of participants had, at some point, undergone CAM therapy and that approximately 36.2% of these believed that the therapy was effective. Respondents cited safety, convenience, and low price as the main reasons for using CAM [17]. In a 2018 survey of allergists, 81% responded that they had patients who use CAM therapies and that patients use CAM therapies more often than vitamin supplements [18]. The chronic nature of allergic diseases and the paucity of preventive or curative treatments also stimulate interest in CAM therapies [19].

Given the popularity of CAM treatments, high-quality data about these therapies are needed to establish professional practice guidelines. In the United States, the National Center for Complementary and Integrative Health has been tasked with evaluating the mechanisms, efficacy, and safety of botanical medicines through basic science studies, clinical research, and the establishment of dedicated botanical research centers [20]. The design of randomized, placebo-controlled studies in CAM is complicated by difficulties in blinding and the establishment of appropriate placebos, particularly in trials of acupuncture.

Acupuncture is a component of traditional Chinese medicine (TCM) that was originally believed to work on the principle of the redistribution of qi, the life energy. In TCM, disease is understood to originate from an imbalance or poor flow of qi. Acupuncture has long been used in TCM to treat AR, and studies of this treatment have shown mixed results, with the most rigorous studies showing only modest clinical benefits [21–24]. The 2015 revision of the American Academy of Otolaryngology-Head and Neck Surgery clinical practice guidelines for AR cites a low level of confidence in the evidence to support acupuncture as a treatment option. Acupuncture may be a reasonable option for patients with relatively mild symptoms who wish to minimize medication use and who find its cost acceptable [1]. These results have helped practitioners to improve their use of acupuncture to treat AR. However, high-quality scientific evidence is needed to instruct the clinical application of acupuncture.

Preliminary experiments have found that the use of acupuncture at three nasal acupoints plus acupoint application (AAP) achieve a more persistent effect in the treatment of AR than simple acupuncture alone. Based on this preliminary research, a multicenter, randomized controlled trial (RCT) has been designed in which acupuncture at nonmeridian acupoints and sham AAP will be used with a control group to evaluate the effect of AAP through long-term observation. The purpose of this trial is to answer three questions: (1) Does AAP benefit PAR? (2) How long do the effects last? and (3) Does AAP work by intervening peripheral blood IL-4, IL-5, IL-6, IL-8, and IL-10 levels? Similar research techniques have been applied in previous studies on PAR such as the Total Nasal Symptom Score (TNSS) [25], visual analog scale (VAS) [26], and Total Non-Nasal Symptom Score (TNNSS) [22]. This trial has adopted TNSS, VAS, and TNNSS due to their wide applicability. The trial hypothesis is that AAP will achieve equal or better long-term symptom relief in PAR or severe AR and reduce its recurrence compared to acupuncture alone.

The trial has been registered at acmctr.org AMCTR-ICR-18000179.

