## Methods/design

### Design

The study is designed as a multicenter, parallel-group, randomized, and single-blind trial to compare AAP with a sham acupuncture for PAR treatment. The trial was designed according to the Standard Protocol Items: Recommendations for Interventional Trials (SPIRIT) statement (Fig. 2) [27], and conforms to the Consolidated Standards of Reporting Trials (CONSORT 2010) guidelines (Fig. 1) and Standards for Reporting Interventions in Controlled Trials of Acupuncture (STRICTA) [28, 29].

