#### Control group

The control group will receive shallow needling at sham Yintang (EX-HN3), sham Yingxiang (LI20), sham Shangyingxiang (EX-HN8), sham Feishu (BL13), sham Dazhu (BL11), and sham Taiyuan (LU9). Each of these acupoints is a nonacupoint located at a different physical location to the actual acupoints. The placebo ointment is composed of buckwheat powder and coke, resulting in an ointment appearing similar to the AAP ointment.

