### Statistical analysis

#### Sample size calculation

The trial will test two groups in parallel. Sample size calculation was performed using SAS 9.3 (SAS Institute Inc., Cary, NC, USA) at the Clinical Evaluation Center of First People’s Hospital Affiliated to Shanghai Jiaotong University. The mean change in TNSS before and after treatment was used as the indicator of efficacy evaluation in sample size calculation. Other research has shown a mean TNSS change of 2.53 ± 4.74 after acupuncture treatment [22] and 2.75 ± 1.06 after AAP [35]. Based on these findings, the appropriate trial sample size with power of 80%, alpha value of 0.05, and acceptable delta value of 0.2 was calculated. The results show that a clinically important difference can be detected by a sample size with at least 49 in each group. Accordingly, this number was increased to 60 per group (a total of 120) to allow for a predicted 20% dropout rate.

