## Discussion

Acupuncture is an important component of TCM. It is technically simple to perform and easy to teach. Research has indicated that acupuncture alleviates symptoms of PAR and improves quality of life [36]. However, few high-quality studies support the technique in this regard [37]. Standardized acupuncture treatment protocol and scoring system are currently not available; therefore, it is difficult to draw conclusive evidence through systemic review and meta-analysis [36]. Procedure and therapeutic effects of acupuncture are based on thousands of years of empirical practice. With the worldwide applications of acupuncture, advanced molecular biology methods have been used to explore the mechanism. However, because TCM is based on a different philosophy to biomedicine, incorporating acupuncture into treatment regimens remains difficult. Nevertheless, recent advances in neuroendocrinology and immunology have allowed a better understanding of acupuncture. The results of this trial will help determine whether this treatment should be more widely applied in clinical practice.

In the preliminary experiment, a pilot RCT was conducted using a small sample with the aim of testing the feasibility of the trial. Participants were divided into three groups of 20. The first group underwent AAP, the second underwent acupuncture only, and the third underwent loratadine therapy. The results showed that AAP achieved a more persistent effect than acupuncture or loratadine therapy alone. This trial intends to use this multicenter RCT to provide reliable evidence for the short-term and long-term efficacy of AAP. This will be compared with a control group of acupuncture at nonmeridian acupoints and sham AAP in the treatment of AR. The trial will evaluate differences in the short-term and long-term effects of AAP and whether this treatment can affect peripheral blood IL-4, IL-5, IL-6, IL-8, and IL-10 levels. TNSS determined at the end of the 4-week treatment will be taken as the primary outcome of the trial. This will enable further integration of acupuncture into the current scientific practice. Therefore, the trial presents a promising new approach to the fusion of acupuncture and biomedicine using AAP as an example.

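### The stated trial hypothesis (AAP at least as good as acupuncture alone) does not match the randomised comparison, which is AAP against sham needling plus placebo ointment

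*Protocol article*

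**What the plan says.** The last part of the Background gives the trial hypothesis: "AAP will achieve equal or better long-term symptom relief in PAR or severe AR and reduce its recurrence compared to acupuncture alone". Shortly before it, the same section lists three questions: whether AAP benefits perennial allergic rhinitis, how long the effect lasts, and whether it acts through interleukin levels.

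The Design section describes a parallel-group trial "to compare AAP with a sham acupuncture for PAR treatment". Randomization is 1:1 to two groups. Under Control group: "The control group will receive shallow needling at sham Yintang (EX-HN3), sham Yingxiang (LI20), sham Shangyingxiang (EX-HN8"), followed by further sham points. Of these it says "Each of these acupoints is a nonacupoint located at a different physical location to the actual acupoints". On the patch it says "The placebo ointment is composed of buckwheat powder and coke". The Discussion repeats the contrast: "This will be compared with a control group of acupuncture at nonmeridian acupoints and sham AAP in the treatment of AR".

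The Sample size calculation takes its inputs from other studies: "a mean TNSS change of 2.53 ± 4.74 after acupuncture treatment [22] and 2.75 ± 1.06 after AAP [35"]. It adds 80% power, alpha 0.05 and a delta of 0.2 whose role is not explained, and arrives at 49 per group, raised to 60.

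The primary outcome is the TNSS change from baseline to the end of the 4-week treatment. TNSS change at 2 weeks and at 1, 3 and 6 months is secondary. Efficacy analysis names a two-sample t test or Wilcoxon rank-sum test at p < 0.05, and repeated measures analysis of variance for repeated data.

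**The concern.** The hypothesis names one comparator and the trial randomises another. AAP against sham needling with a placebo ointment estimates the effect of the whole package, needling and herbal patch together. It gives no randomised estimate of what the patch adds to genuine acupuncture, which is what a comparison with acupuncture alone would measure.

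The form of the claim does not fit the test either. A claim of being at least as good is a non-inferiority claim and needs a margin; a difference test at p < 0.05 cannot establish it.

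What the trial may conclude is at stake. While the sentence stands, a positive result can be reported as AAP beating acupuncture, and a non-significant one as AAP equalling it. Neither conclusion would follow from the data.

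**Working it through.** **1. Comparator, section by section**

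| Section | Comparator of AAP |
|---|---|
| Background, hypothesis sentence | acupuncture alone |
| Abstract; Background, design sentence; Discussion | acupuncture at nonmeridian points plus sham AAP |
| Design | sham acupuncture |
| Control group | shallow needling at non-acupoints, placebo ointment |
| Sample size calculation, inputs | acupuncture (no sham value) |
| Discussion, pilot | acupuncture only and loratadine (three groups of 20) |

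An acupuncture-only group existed in the pilot but not in this trial. The hypothesis sentence and the sample-size inputs are out of line with the rest.

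**2. Form of the test.** The t test, the Wilcoxon test and the repeated measures analysis are all tests of difference. No non-inferiority or equivalence test is named. The delta of 0.2 is not called a margin. If it were one, it would have no acupuncture-alone arm to apply to.

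**3. The plan's figure of 49.** The two quoted means differ by 2.75 − 2.53 = 0.22. That subtraction is made here; the article does not state it as the planning effect. For a two-sided difference test, n per group = 2 × SD² × (1.96 + 0.84)² / d²; the results below use unrounded quantiles:

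- SD 1.06, d = 0.22: 365
- SD 4.74, d = 0.22: 7288

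Reading 0.2 as a non-inferiority margin in TNSS points (an assumption), with one-sided alpha 0.025, the same formula applies with d equal to the margin plus any true benefit:

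- true difference 0 (d = 0.2): 441 (SD 1.06) to 8818 (SD 4.74)
- true benefit 0.22 (d = 0.42): 100 to 2000

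None of these gives 49. That is a separate problem and the present point does not depend on it. It does show that treating 0.2 as a margin would not explain the sample size.

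**4. What a null result could show.** The article gives no SD for AAP against sham. Assume that each quoted SD in turn holds in both arms. The 95% half-width is 1.98 × SD × √(2/n), with n = 49:

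- SD 1.06: 1.98 × 1.06 × 0.202 = 0.42
- SD 4.74: 1.98 × 4.74 × 0.202 = 1.90
- root mean square of the two, √[(4.74² + 1.06²)/2] = 3.43: 1.98 × 3.43 × 0.202 = 1.37

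With all 60 per arm, √(2/60) = 0.183 and the range is 0.38 to 1.72. Even the most favourable value is nearly twice 0.2.

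**5. Endpoints.** Long-term TNSS is a listed secondary outcome, so durability against sham can be examined. Recurrence does not appear under Primary or Secondary outcome measures.

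**The case against.** The strongest reply is that one Background sentence is being weighed against a design that is otherwise coherent. The same section sets out the trial's purpose as three questions, and the first two, benefit and duration, can be tested against sham. The Abstract, Design and Discussion all name the sham comparator. A week-4 primary outcome with follow-up outcomes at 1, 3 and 6 months is a legitimate choice. This stands. A reader might infer that the trial cannot answer any of its questions, or that long-term relief goes unmeasured; the document supports neither reading.

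Two further replies carry weight. First, 0.22 is not stated as the planning effect, and since it does not lead to 49, the text does not show that it was used. What can be said is that the quoted inputs are acupuncture and AAP changes. Second, the article refers to a full protocol that is not shown, so a definition of recurrence may exist there; only its absence from the listed outcomes is visible.

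The risk of misreporting is a prediction. Still, the article calls this sentence the trial hypothesis, and the same comparator recurs in the sample-size inputs, so it is more than a stray phrase. No analysis plan can supply an arm that was not randomised.

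**Conclusion.** The point holds for the hypothesis sentence and for the sample-size inputs. As written, the hypothesis cannot be tested: no participant receives acupuncture alone, the planned tests are tests of difference, and no margin is identified. The comparison of AAP with sham is sound in principle and can answer whether the package works and how long the effect lasts.

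On size, a non-significant result with 49 per arm would leave an uncertainty of about ±0.4 to ±1.9 TNSS points, so it could not support equality within 0.2 even against sham. That range assumes that one of the two quoted SDs applies to both arms. Neither is documented for this contrast. The comparator mismatch does not depend on any of these figures.

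**What to change.** Because the Trial status section says recruitment has begun, make the change by a dated, openly reported amendment:

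- State the primary hypothesis as AAP being superior to sham needling plus placebo ointment on TNSS change from baseline to week 4. Make durability at 1, 3 and 6 months secondary.
- Remove the equal-or-better wording and the reference to acupuncture alone.
- Remove recurrence, or label it exploratory and define it from the TNSS and medication records already collected.
- State that conclusions concern the whole package against sham, and that a non-significant result will not be read as equality.
- In the Sample size calculation, state that the quoted acupuncture and AAP changes do not describe the sham contrast.

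The cost is an amendment and a narrower claim: the trial would no longer offer evidence on AAP against acupuncture alone. No arm, patients or data are added. The irreproducible 49 needs its own correction, which this rewording does not provide.

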## Methods/design

### Design

The study is designed as a multicenter, parallel-group, randomized, and single-blind trial to compare AAP with a sham acupuncture for PAR treatment. The trial was designed according to the Standard Protocol Items: Recommendations for Interventional Trials (SPIRIT) statement (Fig. 2) [27], and conforms to the Consolidated Standards of Reporting Trials (CONSORT 2010) guidelines (Fig. 1) and Standards for Reporting Interventions in Controlled Trials of Acupuncture (STRICTA) [28, 29].

**Fig. 1 Fig1:**
[figure not shown]
CONSORT flow diagram

To achieve the targeted enrollment of participants, clinical recruitment flyers will be placed at three hospitals. Clinical recruitment staffs are responsible for enrolling 120 participants with moderate-to-severe PAR. Participants will be screened based on inclusion and exclusion criteria. All participants will be briefed on the purpose, procedures, treatments, and possible risks of the trial; and will be clearly informed of their rights to discontinue participation at any point. Screening will take approximately 1 week. During this period, participants will be asked to complete questionnaires related to their symptoms. Once participants have signed consent forms, they will be randomized to receive 12 sessions of AAP or sham acupuncture and AAP for 4 weeks.

The trial design flowchart is presented in Fig. 1, and the trial design schedule is shown in Table 1.

**Table 1 Tab1:** Trial design schedule

Period	Screening	Baseline	Treatment(W1–4)		Follow-up(W5-M6)	
Time	W-1	W0	W2	W4	M3	M6
Eligibility	X					
Demography and medical history	X					
Physical examination	X					
Informed consent	X					
TNSS	X	X	X	X	X	X
VAS	X	X	X	X	X	X
TNNSS	X	X	X	X	X	X
Adverse event			X	X		
Medication use	X	X	X	X	X	X
Compliance			X	X	X	X

*TNSS* Total Nasal Symptom Score, *VAS* visual analog scale, and *TNNSS* Total Non-Nasal Symptom Score

### Trial participants

The trial will recruit inpatients from the three trial locations admitted from January 2018 to June 2020. To ensure that results are accurate, the trial will include strict inclusion, exclusion, and elimination criteria, as outlined below.

### Inclusion criteria

Participants are considered eligible if they meet all of the following criteria: (1) meet the diagnostic criteria for moderate-to-severe PAR, (2) meet the diagnostic criteria for PAR lung Qi deficiency and cold syndrome, (3) any gender, aged 18–60 years old, (4) PAR that could be distinguished from cold or tetanus-related motor rhinitis, and (5) agree to participate in the trial with providence of informed consent.

### Exclusion criteria

Participants will be excluded if they meet any of the following criteria: (1) does not meet the diagnostic criteria for PAR; (2) presence of rhinosinusitis, sinusitis, and nasal septal deviation as comorbidities; (3) presence of severe respiratory illness, circulatory disease, digestive disease, urinary system disease, hematologic disease, nervous system disease, endocrine disease, mental disorder, or malignant tumor as comorbidities; (4) underwent antibiotic treatments for upper respiratory tract infection or paranasal sinusitis in the 2 weeks prior to the start of the trial; (5) pregnant or lactating women; (6) presence of skin lesions or scars on the AAP acupoint; (7) particularly sensitivity to drugs or dressings; (8) pretreatment TNSS of < 4; and (9) presence of alcoholism, which cannot be terminated during the experiment.

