### Blinding

This will be a single-blind trial. All participants will be treated separately to prevent communication. Except acupuncturists, all relevant parties will be blinded to the intervention groups. Treatments will be administered by two acupuncturists using treatment patches prepared by operational assistants. Due to the nature of AAP, it is difficult to fully ensure blinding among participants allocated to either group. Participants will be required to wait for 120 min in a room, after which their treatment patches will be removed by research nurses. In addition, acupuncturists, operational assistants, and research nurses are instructed to not communicate with participants on any information that might alert them to which group they have been allocated. Participants will be informed that they have an equal chance of allocation to the treatment or control group before research participation. The participants will be blinded to the group they belong to because needle penetration is achieved in all cases. In addition, outcome evaluators and statistical analysts will be blinded to the groupings and will not be involved in any part of the treatments during trial to ensure no statistical bias in the results.

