### Outcome measures

#### Baseline information

Demographic information will be collected using a custom-made, standardized survey form that includes the following items: center location, name, age, sex, address, telephone number, and employment. A custom-made form will be used to collect medical information including diagnosis, nasal mucosal examination result, allergen examination result, typical symptoms, occurrence time of symptoms, accessory examination of nasal mucosa and nasal sinus, relevant diseases (allergic asthma and allergic conjunctivitis), and medication history.

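### The entry rules do not name allergy to the placebo ointment's buckwheat ingredient, so an allergic control could be exposed to it repeatedly and the sham may not be inert for that person

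*Protocol article*

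**What the plan says.** - **Entry rule.** Item (7) under Exclusion criteria is the only one about sensitivity to what is applied: "particularly sensitivity to drugs or dressings". No item mentions food allergy, buckwheat or the ingredients of either ointment.
- **Placebo.** Under Control group: "The placebo ointment is composed of buckwheat powder and coke, resulting in an ointment appearing similar to the AAP ointment".
- **Population.** The Background defines allergic rhinitis as a "symptomatic nasal disorder resulting from an IgE-mediated immunological reaction to allergen exposure". Inclusion criterion (1) requires moderate-to-severe perennial disease.
- **Exposure.** The Intervention section sets 12 sessions over 4 weeks for both arms. The Blinding section adds: "Participants will be required to wait for 120 min in a room, after which their treatment patches will be removed by research nurses". The Treatment group text gives about 3 g of ointment per acupoint at six acupoints and calls the placebo matching. It gives no separate quantity for the placebo.
- **Allergen testing.** The baseline form under Outcome measures records "diagnosis, nasal mucosal examination result, allergen examination result, typical symptoms". The panel is not stated, and no entry rule refers to the result.

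**The concern.** A sham ointment should do nothing. Buckwheat is a food protein source to which some people are allergic, and the trial enrols only people with allergic disease. A screener who asks about drugs and dressings would not reliably bring out a food allergy. The printed criteria therefore leave room for a buckwheat-allergic person to be randomised to repeated skin contact with that allergen.

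The first thing at stake is that participant's safety. The second is the meaning of the control arm, because for such a person the comparison is no longer with an inert ointment. In principle a reaction could also affect the nasal score, the cytokine levels or the count of skin reactions in the control arm.

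**Working it through.** The plan gives no figure on this point to reproduce. The working sets the sections side by side and then bounds the possible effect under stated assumptions.

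**1. Is there a gap in the entry rules?** The ingredient (Control group), the allergic population (Background, Inclusion criteria) and the repeated exposure (Intervention, Blinding) are all stated. Exclusion (7) names two categories, and a food powder falls clearly in neither. The allergen result is collected but not used for eligibility. The gap is real on the printed text. If the placebo quantity matches the active ointment (assumption), the exposure is 6 × 3 g = 18 g per session.

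**2. How many controls might be affected?** The protocol gives no rate, so the allergic share s is assumed to lie between 0.1% and 5%. With 60 controls, the expected number is 60 × s and the chance of at least one is 1 − (1 − s)^60. If each affected control scores w TNSS points worse (assumed 2 to 6), the control mean moves by s × w.

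| s | expected of 60 | chance of at least one | shift, w = 2 | w = 4 | w = 6 |
|---|---|---|---|---|---|
| 0.1% | 0.06 | 6% | 0.002 | 0.004 | 0.006 |
| 0.5% | 0.3 | 26% | 0.01 | 0.02 | 0.03 |
| 1% | 0.6 | 45% | 0.02 | 0.04 | 0.06 |
| 2% | 1.2 | 70% | 0.04 | 0.08 | 0.12 |
| 5% | 3 | 95% | 0.10 | 0.20 | 0.30 |

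These shifts assume that every allergic control develops a nasal response to a skin patch. The protocol documents no such response, so they are upper bounds for each s and w.

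**3. How large is that against the noise?** The Sample size section quotes SDs of 4.74 and 1.06. The pooled SD is √((4.74² + 1.06²)/2) = 3.43. With 60 per arm, the standard error of the difference is 3.43 × √(2/60) = 0.63. A shift of 0.20 is 0.20/0.63 = 0.32 standard errors. Even a shift of 0.30 raises the two-sided type I error only from 0.050 to 0.077 (normal approximation). If the true SD were as small as 1.06, the error would be at most 0.061 for s up to 1%, but 0.34 at s = 5% and w = 6. The effect could matter only where a high allergic share, a strong nasal response and a small SD coincide.

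**4. Which way would it go?**
- If a reacting control stays in and scores worse, as the intention-to-treat statement under Efficacy analysis implies, the difference grows in favour of the active arm.
- If that person discontinues, the Follow-up section removes the participant together with the latest data, and the reaction never enters the comparison.
- Rescue medicine, allowed under Concomitant care, could lower that person's score.
- The active ointment contains seven listed herbs and ginger juice, and the only application reactions the protocol lists are for the active treatment. A reaction in that arm could push the other way.

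**5. Would the safety reporting catch it?** The Safety assessment section defines an adverse event as one symptom shared by four or more participants. The expected number of affected controls is at most 3 across the assumed range. Isolated placebo reactions could go uncounted, which favours screening at entry.

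**The case against.** The case against has several parts.

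- **Outside knowledge.** No section says that buckwheat is allergenic or reports a reaction to the placebo. This is true. That buckwheat can sensitise is ordinary general knowledge, labelled as such here, and no rate is drawn from it except as an assumption. The gap in the entry rule can be seen from the text.
- **Exclusion (7) may already cover it.** Both ointments come from a hospital pharmaceutical department and are applied on fabric, so the item could be read to include the patches. That reading is possible but not reliable for eliciting a food allergy. The stated compliance with regulatory guidance concerns the product and does not say who may safely receive it.
- **The full protocol or screening forms may already ask.** They are not shown, and the article says that the exclusion criteria were revised. If the question is there, the fix reduces to confirming it.
- **The allergen examination cannot be relied on.** This stands in full. With no panel stated, it cannot be assumed to test for buckwheat, so a history question must carry the screen.

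A reader might go further and infer that the treatment effect is inflated, perhaps by setting the shift against the 0.22-point gap in the planning figures (2.75 − 2.53). Shifts of 0.01 to 0.20 would then look like 5% to 91% of the effect. The documents do not support this. The 0.22 is the gap between two outside studies, of acupuncture and of the active combination, and is not an expected difference from sham. No section gives a sensitisation rate or a nasal response to a 120-minute patch, and step 4 shows that the direction is open.

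**Conclusion.** The point holds as a safety gap in a stated entry rule, with a secondary doubt about whether the sham is inert for an allergic participant. It rests on the printed ingredient, population, exposure and exclusion list, plus the general knowledge that buckwheat can sensitise. One affected person is enough to justify the change. Under an assumed allergic share of 0.1% to 5%, the chance of at least one such control is 6% to 95%.

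Any effect on the TNSS comparison is a possibility only. At a share of 1% or less it is at most 0.06 points. At 5% and 4 points each it is 0.20, about a third of the standard error at the pooled SD. Its direction is not settled, and the documents do not establish a biased treatment effect.

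**What to change.** Extend exclusion (7) so that, besides the sensitivities it already names, it covers *known or suspected allergy to any ingredient of either ointment, including buckwheat*. Apply it before randomisation through one history question. Use the allergen examination result for this purpose only if its panel covers the ingredient concerned.

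Recruitment has begun, so participants already randomised stay in the intention-to-treat analysis whatever their answer.

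The cost is a one-line amendment and one screening question. The downside is the loss of a few otherwise eligible people: 120 × 0.1% to 120 × 5%, or about 0.1 to 6 per 120 for buckwheat under the assumed range. Allergy to ingredients of the active ointment could add to this, by a number the documents do not allow one to estimate.
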